### Exclusion criteria

2.7

The study exclusion criteria are as follows:

(1)Patients who have previously taken 5-ALA/SFC within 8 weeks before obtaining an informed consent(2)Patients treated with metformin(3)Patients with a history of porphyria, hemochromatosis, or viral hepatitis(4)Women who are currently pregnant or lactating(5)Patients will not be compliant with a medically approved contraceptive regimen during the study period(6)Patients who participated in another clinical study within the past 4 months(7)Patients whom the investigators consider inappropriate for participation

### Withdrawal criteria

2.8

A patient may be withdrawn from the study prematurely for the following reasons:The patient asks to leave the trial.Continuing participation is inadvisable due to one or more adverse events.5-ALA/SFC must be withdrawn for ≥4 weeks for any reason(s).The patient becomes pregnant.In the investigator's opinion, continuation in the trial would be detrimental to the patient's well-being.

### Study protocol

2.9

Participants with MDM will be administered 5-ALA/SFC 100 mg twice a day (200 mg/d) for 24 weeks. An investigator will explain the study protocol to each patient and, if consent is obtained, the investigator will perform the observation/examination at the time of registration in accordance with the description in Figure 1. According to the inclusion and exclusion criteria, the investigator will submit the participant's registration form to the study secretariat at the Department of Endocrinology and Metabolism, Nagasaki University Hospital.

**Figure 1 F1:**
[figure not shown]
Treatment schedule and outcome measures. FGM = flash glucose monitoring, OGTT = oral glucose tolerance test.

After the visit date, the investigator will continue to administer 5-ALA/SFC and conduct necessary examinations and surveys until week 24 in accordance with the schedule in Figure 1. The investigator will refer to the patient's FGM result to adjust the insulin dose based on his/her own judgement. During the study period, any change of the drug or dose of antidiabetic agents (except insulin) is prohibited.

To evaluate the patients’ glucose-dependent insulin responses, a 75-g OGTT will be performed twice: before the start of the 5-ALA/SFC regimen (week 0, 1st OGTT) and at 24 weeks after the start of the 5-ALA/SFC regimen (week 24, 2nd OGTT). When patients need to be withdrawn from the study for any reason, they will undergo 75-g OGTT after discontinuing the 5-ALA/SFC. Both OGTTs will be carried out under the condition of overnight fasting. All antidiabetic agents including insulin and 5-ALA/SFC will be held until the preceding day in each OGTT.

### Laboratory measurements

2.10

The 2 OGTTs will use a 75-g glucose formulation, Trelan-G75 (AY Pharma, Tokyo). For each OGTT, the levels of plasma glucose (mg/dL), serum insulin (μU/mL), serum C-peptide (ng/mL), and plasma glucagon (pg/mL) will be measured at fasting (0 minutes) and at 30, 60, 120 minutes after the ingestion of the glucose load. We will also measure the serum levels of glycated albumin, nonesterified fatty acid, leptin, adiponectin, high-molecular-weight adiponectin, iron, unsaturated iron-binding capacity, and ferritin at 0 minutes. Urine specimens will be obtained on each OGTT day for the measurement of the patient's albumin/creatinine ratio.

The levels of serum insulin and C-peptide will be measured by the ECLusys kit (Roche, Basel, Switzerland). Blood samples for plasma glucagon will be obtained using BD P800 tubes (BD, Franklin Lakes, NJ). Plasma glucagon will be measured by a sandwich ELISA kit (Mercodia, Uppsala, Sweden).

As shown in Figure 1, we will measure the patient's complete blood count and serum (plasma) levels of sodium, potassium, chlorine, total cholesterol, high-density lipoprotein, cholesterol, low-density lipoprotein, blood urea nitrogen, creatinine, total bilirubin, aspartate aminotransferase, alanine aminotransferase, alkaline phosphatase, γ-glutamyl transpeptidase, creatine kinase, glucose, and glycated hemoglobin at every visit of the study (week 0, 4, 8, 16, and 24), and (if withdrawing from the study) at early discontinuation.

### Adverse events

2.11

A serious adverse event is defined as any untoward medical event that occurs at any dose, results in death, a life-threatening condition, requires hospitalization, and results in significant disability or incapacity.

All serious adverse events occurring between the signing of the informed consent form and the end of the trial will be documented in the medical records and reported to the Minister of Health, Labor, and Welfare (Japan) and the CRB by the responsible investigator in accordance with Japanese regulations.

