#### Safety endpoints

2.4.3

All adverse events that occurred during the trial will be recorded.

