### Statistical analysis

2.13

The respective analysis sets are defined as follows. The intention to treat (ITT) population is defined as all participants registered for this trial; the safety analysis set (SAS) population is defined as the participants in the ITT population with at least 1 administration of 5-ALA/SFC. The full analysis set (FAS) population is defined as the participants in the SAS for whom data after the administration of 5-ALA/SFC at one or more scheduled visits are available. The per protocol set (PPS) is defined as the participants in the FAS with the primary outcome measure.

The characteristics of all 5-ALA/SFC-treated populations will be summarized using descriptive statistics on the ITT, SAS, FAS, and PPS.

An efficacy analysis will be conducted using the FAS and PPS. The primary endpoint and secondary endpoints listed above in Section 2.4 will be estimated as point estimates and 95% confidence intervals and summarized using descriptive statistics.

Safety endpoints will be analyzed in the SAS population. Adverse events will be stratified by serious versus nonserious, causal relationship, severity, and outcome. Analyses will be categorized and tabulated, and a list will be formulated including causality, extent, and outcomes.

Data containing missing values will be also included in the analysis. Missing values will be imputed by a last observation carried forward analysis. All data will be analyzed after being fixed/set. All tests of significance will be done at a 2-tailed significance level of 0.05. Data relevant to this clinical trial will be analyzed using SAS, SPSS, R software, or JMP Pro 15 or higher.

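### The definition of a serious adverse event joins its criteria with *and*, so as printed one criterion is not enough to make an event serious

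*Protocol article*

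**What the plan says.** Section 2.11 (Adverse events) opens the definition with "A serious adverse event is defined as any untoward medical event that occurs at any dose" and goes on to the outcome criteria: "results in death, a life-threatening condition, requires hospitalization, and results in significant disability or incapacity". The only *or* is inside the last criterion, between disability and incapacity.

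The term is then used in two places:

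- **Reporting (section 2.11).** The duty covers "All serious adverse events occurring between the signing of the informed consent form and the end of the trial". Reports go to the health minister and the certified review board "by the responsible investigator in accordance with Japanese regulations".
- **Analysis (section 2.13, Statistical analysis).** "Adverse events will be stratified by serious versus nonserious, causal relationship, severity, and outcome". No second definition of seriousness is given there.

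Section 2.4.3 (Safety endpoints) states separately: "All adverse events that occurred during the trial will be recorded".

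**The concern.** A definition of seriousness is a classification rule: an investigator takes an event, compares it with the criteria and gives it a label. With the criteria joined by *and*, the printed rule asks for all of them together. An event that meets exactly one, such as an admission followed by full recovery, fails it.

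Two things depend on the label. One is the serious/nonserious split in the safety analysis, for which the article offers no other test. The other is the reporting sentence, whose subject is serious adverse events as just defined. Safety is one of the trial's two declared aims, alongside effectiveness, so the rule that sorts its safety events should be usable as written. If each investigator must guess the intended rule, events may be labelled inconsistently.

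**Working it through.** The plan gives no figure on this point, so there is none to reproduce. The check is to read the definition as a logical rule.

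**Inputs (section 2.11).** Four outcome criteria, each met or not met:

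- D: death
- L: life-threatening condition
- H: hospitalization required
- I: significant disability or incapacity

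**Step 1. Count the patterns.** Four yes/no criteria give 2 × 2 × 2 × 2 = 16 patterns.

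**Step 2. Apply each rule.**

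- As printed (D and L and H and I): only the pattern with all four met is serious, 1 of 16.
- Any one sufficient (D or L or H or I): every pattern except the one with none met is serious, 16 − 1 = 15 of 16.

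The two rules agree on 2 patterns (all met, none met) and disagree on 15 − 1 = 14. The patterns are not equally likely and some hardly occur, so these counts describe the rules and say nothing about event frequency.

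**Step 3. Try concrete events.**

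| Event | Criteria met | As printed | Any one sufficient |
|---|---|---|---|
| Admission, full recovery | H | nonserious | serious |
| Life-threatening event, treated without admission, full recovery | L | nonserious | serious |
| Lasting disability, no admission | I | nonserious | serious |
| Death outside hospital, no preceding disability | D, L | nonserious | serious |

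**Step 4. Look for text that rescues the printed rule.** Neither section 2.11 nor section 2.13 says that one criterion suffices. Section 2.4.3 ensures that events are recorded but not how they are labelled. Severity is a separate stratum in section 2.13 and does not stand in for seriousness. The reference to Japanese regulations governs how reports are made; it does not restate the definition and does not extend to the analysis.

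**The case against.** The strongest reply is that nobody would apply the sentence literally. A single event that is fatal, needs admission and also leaves disability makes little sense as a joint requirement. The list is also grammatically uneven, which points to loosely worded categories and not to a deliberate rule. That reply stands as to intent: this is most plausibly a slip. It does not make the printed sentence correct. Nor is it explained by the article being a condensed protocol, since shortening a list does not change its connective.

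The second reply is that the consequences are contained. This largely stands. All adverse events are recorded; section 2.13 also sorts them by causal relationship, severity and outcome and adds a listing; reporting is tied to Japanese regulations; and no hypothesis or stopping rule uses a count of serious events. In a five-patient study, a death or an admission would be visible in the listing even if mislabelled.

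Three stronger readings are tempting, and the documents support none of them:

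- **That almost no event would be reported.** This overlooks the reference to regulations. The article also gives no event rate from which to derive an expected count, and with five patients the count could be zero under either wording.
- **That one mislabelled event has a measurable effect of 1/5 = 20 percentage points.** That is true of any yes/no item in five patients and does not measure this defect. Section 2.13 plans tabulation and listing of adverse events and names no serious-event rate to be estimated.
- **That the list omits criteria it ought to contain, for example a birth outcome, because "The patient becomes pregnant" is a withdrawal reason in section 2.8.** The article does not show the standard against which the list would be incomplete, and a fuller list may stand in the full protocol. Naming pregnancy as a reason for withdrawal does not contradict the list of criteria.

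**Conclusion.** The definition in section 2.11 is wrong as written. It requires all its criteria jointly, and it is the only definition behind both the reporting sentence and the serious/nonserious stratification. Followed to the letter, it classes a non-fatal admission, or a death without admission, as nonserious.

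The defect is small in practice: it affects the labelling of events, not whether they are captured, and it touches no efficacy analysis. This conclusion assumes that the article reproduces the operative wording of the protocol. If the full protocol already says that any one criterion suffices, only the article needs correcting.

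**What to change.** Restate the definition in section 2.11 so that an event is serious if it meets **any one** of the listed criteria: death, life-threatening condition, hospitalization, or significant disability or incapacity. Set them out as separate items under a lead-in that says one is enough. Replacing *and* by *or* in the existing sentence is not sufficient, because the phrase about occurring at any dose sits in the same series and could then be read as a criterion sufficient by itself. It belongs in the lead-in.

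State in section 2.13 that the serious/nonserious stratification uses this definition, and carry the same wording into the guidance for the case report form. First check the full protocol to see whether the slip is there or only in the article.

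The cost is one sentence plus a cross-reference, with possibly a few more events classed as serious. No endpoint, analysis set or efficacy estimate changes.

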### Data collection and management

2.12

The sponsor-investigator and sub-investigators will fill in all of each patient's data in a case report form (CRF). It is necessary that all data recorded in the CRF are consistent with the original material, unless data recorded directly in the CRF are used as the source material. For the results of FGM, the output data signed by the investigator will be regarded as the original material. During the study, the investigators will collect data at each visit in accord with the schedule in Figure 1. All data recorded in the CRF will be checked by the data manager and will then be fixed/set. All study findings and documents will be made confidential, and patients will always be identified by their patient number, never by name. Confidential patient-identifying documents will be maintained by the investigators to preserve participant anonymity.

During the study, a sponsor-investigator will perform regular site visits to review the protocol compliance, conduct source data verification, assess drug accountability and management, and assess laboratory procedures to ensure that the study is being conducted according to all pertinent requirements.

### Statistical analysis

2.13

The respective analysis sets are defined as follows. The intention to treat (ITT) population is defined as all participants registered for this trial; the safety analysis set (SAS) population is defined as the participants in the ITT population with at least 1 administration of 5-ALA/SFC. The full analysis set (FAS) population is defined as the participants in the SAS for whom data after the administration of 5-ALA/SFC at one or more scheduled visits are available. The per protocol set (PPS) is defined as the participants in the FAS with the primary outcome measure.

The characteristics of all 5-ALA/SFC-treated populations will be summarized using descriptive statistics on the ITT, SAS, FAS, and PPS.

An efficacy analysis will be conducted using the FAS and PPS. The primary endpoint and secondary endpoints listed above in Section 2.4 will be estimated as point estimates and 95% confidence intervals and summarized using descriptive statistics.

Safety endpoints will be analyzed in the SAS population. Adverse events will be stratified by serious versus nonserious, causal relationship, severity, and outcome. Analyses will be categorized and tabulated, and a list will be formulated including causality, extent, and outcomes.

Data containing missing values will be also included in the analysis. Missing values will be imputed by a last observation carried forward analysis. All data will be analyzed after being fixed/set. All tests of significance will be done at a 2-tailed significance level of 0.05. Data relevant to this clinical trial will be analyzed using SAS, SPSS, R software, or JMP Pro 15 or higher.

## Discussion

3

A nationwide case-finding study of genetically defined MDM patients in Japan revealed that 86% of the patients required insulin therapy due to the progressive insulin secretory disorder, and 92% of them had sensorineural deafness.^[1]^ Individuals with MDM have advanced microvascular complications and mitochondria-related complications such as cardiomyopathy, cardiac conductance disorders, neuromuscular symptoms, neuropsychiatric disturbance, and macular pattern dystrophy caused by glycemic variability and higher oxidative stress levels.^[14,15]^ To prevent the development of those complications, therapy in addition to insulin has been desired to directly improve the mitochondrial dysfunction in patients with MDM.

Diagnostic criteria for mitochondrial disease were defined by Japan Intractable Diseases Information Center,^[16]^ but criteria that are specialized for MDM have not been established. We set main criteria as described in the inclusion criteria above based on the results of the nationwide case-finding study.^[1]^ We also set the sub-criteria described above since that study also reported that the rate of a family history of maternal inheritance was 68%,^[1]^ and the Japanese criteria for mitochondrial disease include items such as a high serum lactate level, short stature, cardiomyopathy or cardiac conduction abnormality, and bilateral symmetric abnormal lesions in the basal ganglia and/or brainstem on computed tomography/magnetic resonance imaging.

The administration of 5-ALA to healthy mice activate their mitochondrial respiratory function by increasing the protein expression and activity of cytochrome c oxidase (complex IV).^[6]^ In addition, Shimura et al. recently reported that 5-ALA/SFC increased the oxygen consumption rate and ATP level via an oxidative phosphorylation protein's expression induced by upregulations of heme, heme oxygenase-1, and the mtDNA copy number in skin fibroblasts from individuals with mitochondrial disease.^[17]^

The administration of 5-ALA/SFC reduced blood glucose levels and improved glucose tolerance in diabetic rodents by enhancing mitochondrial function.^[18,19]^ In prediabetic and diabetic human subjects, the oral administration of 5-ALA/SFC also improved their glucose tolerance, although the dosage regimen of 5-ALA/SFC in those studies was lower than that of our present investigation.^[7–10]^ Our study could thus be expected to observe improved effects on insulin secretory capacity and blood glucose regulation by a recovery of the mitochondrial function. For the evaluation of these effect, we will perform a 75-g OGTT before and at 24 weeks after the start of the administration of 5-ALA/SFC and then compare the difference in insulin secretion.

The dosage of the investigational drug will be set at 100 mg taken orally twice daily (200 mg/d) in accord with an ongoing clinical trial for mitochondrial disease. That clinical trial was registered in the Center for Clinical Trials, Japan Medical Association (http://www.jmacct.med.or.jp) as JMA-IIA00358. Another study conducted in patients with type 2 diabetes (ClinicalTrials.gov NCT02481141) demonstrated the safety and tolerability of the dose.^[10]^ In studies using a similar dose of 5-ALA, the adverse events were consistently mild, and some studies did not observe any side effects. We consider that the 200 mg/d dose is acceptable and effective for patients with MDM.

There are some limitations in this trial.

(1)It will be conducted at a single center and the sample size is small (n = 5).(2)It is a single-arm study and lacks a placebo control group.(3)The follow-up period of the trial may be insufficient to lead to a definitive conclusion regarding the improvement of insulin secretion and glycemic control.

Despite these limitations, our research also has strengths. There has been no study assessing the effect of 5-ALA/SFC on insulin secretion and glycemic control in patients with MDM. We may discover an effective antidiabetic agent for MDM according to the pathology.

This trial will evaluate the effectiveness and safety of 5-ALA/SFC in patients with MDM. It will test the potential effectiveness of 5-ALA/SFC as adjunctive therapy for patients with MDM receiving insulin therapy. The findings of the study are expected to provide new treatment options for MDM and improve the glycemic control and prognosis of patients with this disorder.
